#### Secondary outcomes

3.10.3

Prespecified secondary outcomes include the assessment of knee OA symptoms using The Knee Injury and Osteoarthritis Outcome Score (KOOS) knee function subscales including KOOS pain [48], 6-min walk distance, and health-related quality of life measured with the SF-36 questionnaire [49]. Plasma levels of IL-6 by ELISA - a measure of inflammation [12,23], knee compressive force - a measure of knee joint loading measured using gait analysis and musculoskeletal modeling [12,24,50], and self-efficacy for weight loss and exercise [16] are mechanistic secondary outcomes (Table 5). A cost-effectiveness analysis [51] will establish the value of the 48-month D ​+ ​E (diet and exercise) intervention.

**Table 5 tbl5:** Measurements with screening (0 months) and follow-up visits (12, 24, 36, 48 months). Logistics and testing fidelity procedures are located in the Data Management Plan.

Measurements	Explanation	Testing (month)
**Primary Outcome**		
MRI	See Table 4 for details	0, 48
**Secondary Outcomes**		
KOOS pain	The Knee Injury and Osteoarthritis Outcome Score clinical knee pain score [74,75]	0, 12, 24, 36, 48
6-min walk	Measure of mobility	0, 12, 24, 36, 48
Blood biomarkers^a^^,^^b^	Measure of inflammation (IL-6) [76]	0, 48
Gait testing^a^^,^^c^	Measure of knee joint loading [46,77,78]	0, 48
SF-36	Short Form Survey, Health-related quality of life [45]	0, 12, 24, 36, 48
Weight loss self-efficacy, Exercise self-efficacy	Self-efficacy for diet and weight loss (79) and exercise (80)	0, 12, 24, 36, 48
**Questionnaires for Cost Effectiveness Analysis**		
Cost Effectiveness	See Economic Evaluation section for details	0, 12, 24, 36, 48
EuroQol Quality of Life(EQ5D)	Quality of life measure (81) required for the cost effectiveness analysis	0, 12, 24, 36, 48
Work History Resource	Visits to clinicians, tests, medications, injections, surgery, alternative therapies (82)	0, 12, 24, 36, 48
Work Productivity and Activity Impairment Index	To assess absenteeism and presenteeism (82)	0, 12, 24, 36, 48
**Additional Questionnaires**		
Informed Consent		0
Eligibility Questionnaire	To determine eligibility	0
Demographics		0
Medical, Weight History	For eligibility and to document changes in health including frequency of knee pain	0, 12, 24, 36, 48
Medication form	Atherosclerosis Risk in Communities (83)	0, 12, 24, 36, 48
PASE scale	Physical Activity Scale for Elderly (84,85)	0, 12, 24, 36, 48
SWL	Satisfaction with life scale (86)	0, 12, 24, 36, 48
PSS	Perceived stress scale (87)	0, 12, 24, 36, 48
PANAS	Positive and Negative Affect Scale (88)	0, 12, 24, 36, 48
KOOS subscales	KOOS subscales including symptoms, ADL, Sport/Rec [44,74]	0, 12, 24, 36, 48
Safety from Crime	Neighborhood safety (89)	0, 12, 24, 36, 48
Walkability and Exercise Environment Scale	Neighborhood walkability (89)	0, 12, 24, 36, 48
Social Cohesion Scale	Neighborhood social cohesion (90)	0, 12, 24, 36, 48
Dietary screener	Dietary screener from NHANES 2009–2010 (91)	0, 12, 48
Health Literacy	Functional health literacy measure (92)	0
CES-D	Center for Epidemiological Studies Depression (93)	0, 24, 48
Adverse events	Collected as they occur	

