**Table 2 tbl2:** Summary of diet-induced weight loss plan and number of planned contacts.

Months	Weight loss plan	Meal Replacements per day (N)	Contacts per month (N)		
			Total	Individual	Group
0–9	Energy restriction 500–600 ​kcals/day	1–2 (optional)	4	1	3
10–24	Either continued energy restriction or weight loss maintenance once 10 ​% weight loss reached	1 (optional)	2–3^a^	1	2
25–36	Energy restriction/weight-loss maintenance	0–1	1–2^a^	1	1
37–48	Weight-loss maintenance	0–1	1^b^	1	1

a Individual sessions transition to every other month once 10 ​% weight loss is reached.

b Group and individual sessions will alternate every other month.

The exercise component includes two 60-min sessions per week for 48 months. For the first 24 months, participants exercise 2 days/week supervised by study interventionists at one of the designated facilities. For months 25–48, participants wishing to transition to exercise at another location (e.g., home or community gym) will alternate between the supervised facility and a location of their choice during a 2-month transition phase. Previous experience indicates that most participants will choose to maintain the combination of the supervised facility with an alternate location, with about 10 ​% opting for an alternate location entirely [12,26]. The exercise program prescribed to each participant consists of aerobic (15 ​min), resistance-training (20 ​min), a second aerobic (15 ​min), and cool-down (10 ​min) phases. Participants are encouraged to exercise on their own most other days of the week.

Interventionists, trained in validated behavioral change techniques based on a social cognitive theory framework [30], will work with participants in the D ​+ ​E group to gain confidence in their ability to maintain weight-loss for the long-term, maintain exercise independently, and establish a routine of healthy diet behaviors.

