#### Control group

3.6.2

The C group (presented to participants as the Healthy Living Group) is modeled after our previous control groups [23,24,26] and provides attention, social interaction, and lifestyle classes. There will be four, 60-min face-to-face group meetings per year, and quarterly newsletters and text messages to keep the participants engaged. These interactive sessions and the newsletters convey information on topics ranging from medication management, health screenings, menopause, sleep hygiene, to chronic disease management.

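### Adverse events have no scheduled query, while the diet-and-exercise arm has roughly 19 to 33 times the planned face-to-face contact of control, so any between-arm safety comparison risks differential ascertainment

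*Protocol article*

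**What the plan says.** In Table 5 (section 3.10.3, block headed Additional Questionnaires) the adverse-event row reads "Collected as they occur", with no testing month. Almost all other follow-up items in the table carry fixed months. The medical and weight history is taken in both arms at 0, 12, 24, 36 and 48 months, and its stated purpose is "For eligibility and to document changes in health including frequency of knee pain".

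On contact with staff, section 3.6.1 says of the diet-and-exercise arm: "The exercise component includes two 60-min sessions per week for 48 months". Supervision is fixed for the first half: "For the first 24 months, participants exercise 2 days/week supervised by study interventionists at one of the designated facilities". For months 25 to 48 participants may move part or all of their exercise elsewhere, and the authors expect that "most participants will choose to maintain the combination of the supervised facility with an alternate location", with about 10% leaving the facility entirely. Table 2 adds individual and group diet contacts every month. For the control arm, section 3.6.2 says: "There will be four, 60-min face-to-face group meetings per year, and quarterly newsletters and text messages to keep the participants engaged".

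Section 3.11 describes resource-use data from all four centers, with inpatient, emergency and outpatient care among the costs. The article does not link the medical history or the resource-use data to the adverse-event record. Section 3.3 keeps outcome assessors away from intervention visits.

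**The concern.** If an event is recorded when staff learn of it, the number recorded depends on how often a participant meets staff. Here that frequency is set by the randomized arm. A sore shoulder or a minor fall may be mentioned at the next exercise session in one arm, and forgotten before the next quarterly meeting in the other. Blinding of the assessors does not correct this, because what is said at sessions is heard by interventionists, who know the arm.

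A data and safety monitoring board oversees the trial (section 3.1) and the biostatistical team prepares its reports (section 3.5). If those reports or the final paper set adverse events side by side by arm, unequal opportunity to record them could look like an excess caused by the program, or could leave control events under-counted. The events most exposed are those that need no medical care. The primary MRI outcome is not affected.

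**Working it through.** The article states no contact ratio and no safety power, so there is no figure of the plan's own to reproduce. The check is a count of planned contacts.

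**Inputs**
- Exercise (section 3.6.1): 2 sessions a week for 48 months, supervised for the first 24.
- Diet contacts per month (Table 2, total column): 4 in months 0–9, 2–3 in months 10–24, 1–2 in months 25–36, 1 in months 37–48.
- Control (section 3.6.2): 4 meetings a year.

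**First 24 months** (needs no assumption about exercise location)
- Exercise: 2 × 52 × 2 = 208.
- Diet: 9 × 4 + 15 × (2 to 3) = 36 + (30 to 45) = 66 to 81.
- Diet-and-exercise arm: 208 + (66 to 81) = 274 to 289.
- Control: 4 × 2 = 8.
- Ratio: 274/8 = 34.3 to 289/8 = 36.1.

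**All 48 months**
- Diet: 36 + (30 to 45) + 12 × (1 to 2) + 12 × 1 = 90 to 117.
- Control: 4 × 4 = 16.
- The supervised share of the 208 exercise sessions in months 25–48 is not stated, so it is varied:

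| Supervised after month 24 (assumed) | Exercise contacts | Total contacts | Ratio to 16 |
|---|---|---|---|
| none | 208 | 298–325 | 18.6–20.3 |
| half | 312 | 402–429 | 25.1–26.8 |
| all | 416 | 506–533 | 31.6–33.3 |

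**How the ratio moves under other counts**
- Adding the four annual follow-up visits to both arms: (298 + 4)/20 = 15.1 to (533 + 4)/20 = 26.9.
- Counting 16 newsletters and 16 texts as control contacts (taking both as quarterly): 298/48 = 6.2 to 533/48 = 11.1. This is generous to control, since section 3.6.2 presents them as information and engagement, not as health enquiries.

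**What unequal capture could do (illustration only; all risks and capture fractions are assumed)**
Take an equal true risk of 30%, 615 women per arm, and a two-sided 5% comparison of proportions. Recorded risk = true risk × fraction captured.
- 90% vs 90% captured: 27% vs 27%, risk ratio 1.00.
- 90% vs 80%: 27% vs 24%, risk ratio 1.13, chance of p < 0.05 about 23%.
- 90% vs 70%: 27% vs 21%, risk ratio 1.29. Standard error under no difference √(2 × 0.24 × 0.76/615) = 0.0244; under the difference √((0.27 × 0.73 + 0.21 × 0.79)/615) = 0.0243; (0.06 − 1.96 × 0.0244)/0.0243 ≈ 0.50, so the chance of p < 0.05 is about 69%.
- With a 20% true risk, the last two chances are about 15% and 48%.

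**The case against.** The strongest reply is that the quoted cell states timing, not method. It says collection is continuous; it does not say that events are unsolicited or that interventionists gather them. The text after Table 5 lists adverse events among the things assessed by questionnaire, and the table's caption refers logistics to a Data Management Plan that is not shown. A structured query may well exist there. This stands, and the fix allows for it. But the empty month cell is what the article fixes, and followed as written it sets no common occasion on which both arms are asked.

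Second, both arms already have the same annual medical history and medication form, and resource-use data that include hospital and emergency care. This also stands for serious events, many of which would surface either way. It helps less with events that need no care, and the article does not name these sources as feeding the adverse-event record.

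Third, a ratio of contacts is not a ratio of events captured. That is correct. Beyond some frequency, extra contacts add little.

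A reader might infer that adverse events are gathered only by spontaneous report, that the imbalance is about 30-fold throughout, that the comparison is therefore biased, and that the program's safety cannot be judged. The documents do not support this. They never restrict collection to spontaneous report. A 48-month ratio above 30 requires nearly all exercise after month 24 to stay supervised, whereas a mix of locations is expected. They give no capture rates, and they specify no between-arm adverse-event analysis; adverse events lie outside the specific aims.

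**Conclusion.** The point holds as a risk of differential ascertainment, not as a demonstrated bias. The planned opportunity to learn of an event is 34 to 36 times greater in the diet-and-exercise arm during the first 24 months, and about 19 to 33 times greater over 48 months. These are planned contacts, not attended ones, and the longer range rests on the assumed share of supervised exercise in months 25–48. The likely direction is over-recording in the intervention arm relative to control, mainly for non-serious musculoskeletal events and falls. Its size is unknown; the illustration shows only that a modest gap in capture could produce an apparent excess. Serious events are partly protected. It is worth changing because the remedy is inexpensive.

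**What to change.** Keep the ongoing collection. In the adverse-event row of Table 5, add months 12, 24, 36 and 48 and a structured adverse-event questionnaire that is identical in both arms. Have it self-completed, or taken by someone other than the outcome assessors, because answers that mention exercise sessions would reveal the arm.

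State that the between-arm safety comparison rests on these solicited events. Report events volunteered at intervention sessions separately, labeled as unequally ascertained.

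Do not build this on six-month contacts: section 3.11 refers to six-month intervals for resource use, but Table 5 lists the resource forms at the annual visits only.

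If the Data Management Plan already holds such a query, it is enough to show its months in Table 5 and name it as the basis of the comparison.

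The cost is a few minutes at visits that already take place. Annual recall will lose some minor events, but both arms are asked in the same way at the same times.

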**Additional Tests/Imaging**		
Height	To determine BMI	0
Weight	To determine BMI	0, 12, 24, 36, 48
Urine biomarkers^c^	Stored for subsequent analysis	0, 48
Knee PA, Sunrise x-rays	Screen for initial eligibility to undergo MRI exam	0
DXA^d^	To measure changes in body composition and BMD	0, 24, 48

a Methodology for knee joint loading and IL-6 measures can be found in our previous studies [12,20].

b Measured at the 3 US sites (N ​= ​910).

c Measured at the Winston-Salem and Chapel Hill sites (N ​= ​660).

d Measured at the Winston-Salem site (N ​= ​360).

To reduce biomechanical gait variability, a designated tester at each gait testing site (Wake Forest and UNC sites) will assume responsibility for the collection of gait data. To ensure the precision of marker placement and reliability between both sites, test-retest comparisons will be conducted during the 3-month planning period utilizing the same participant with obesity. Furthermore, the Bell regression equation set will be employed to facilitate a more accurate estimation of hip joint centers in participants with obesity [52,53]. All data analyses will be centralized at the Wake Forest location.

Additional measurements that are not included in the specific aims are height and weight, body composition, and questionnaires to assess eligibility, demographics, psychosocial outcomes, social determinants of health, dietary intake, additional KOOS subscales, and adverse events (Table 5).

### Economic evaluation

3.11

A validated computer-simulated model of incident knee OA will establish the cost-effectiveness of this intervention using data from the TOPS trial. The cost-effectiveness ratio provides a measure of value. The cost-effectiveness of a specific prevention or treatment strategy is measured in dollars per quality-adjusted life-year gained ($/QALY). The choice between policy alternatives is best made via incremental analysis, defined as the difference in direct medical costs between two strategies divided by the difference in quality-adjusted life expectancy. To determine how OA prevention-related expenditures compare with other uses of resources, the incremental cost-effectiveness ratios are compared with those in other areas of health care.

If the D ​+ ​E intervention is found to be effective, a budget impact analysis (BIA) of the D ​+ ​E program will quantify the financial consequences of adopting this program by various payer models, including insurance organizations, health care systems, and government. BIA will predict how adoption of the D ​+ ​E intervention will impact the trajectory of spending for people at a high risk for knee OA. These results could be used for budget planning and changes in health insurance premiums. The OAPol model will also quantify the extended financial benefits of weight loss reduction beyond reduction in pain and improvement in functional status, including the reduction in incident cardiovascular disease and type 2 diabetes.

Data are collected from all 4 clinical centers on resource utilization over 6-month intervals for the duration of the intervention and 2 years post-intervention. These data are used as input parameters for a ‘country’ specific analysis using the data from the US to inform US-centered cost-effectiveness analysis, and data from Sydney to inform Australia-centered cost-effectiveness. Direct medical costs include costs of inpatient stays and procedures, emergency department visits, outpatient physician visits as well as costs of laboratory studies, medical devices, and prescription and non-prescription medications. Intervention costs include the cost of meal replacements, progress monitoring, and wages of personnel delivering weight loss, exercise, and weight-loss maintenance interventions over the 4-year intervention period. The cost also includes any facility rental costs required to deliver the intervention.

Direct non-medical costs and indirect costs include the cost of transportation to intervention centers and costs related to the time that study participants need to engage in all TOPS activities. Participant data on lost wages and productivity losses for those working that are related to knee pain are also included in this category.

Utility measures capture patients’ preferences for health states and are scored from 0.00 (death) to 1.00 (perfect health). Utility will be derived from EuroQol (EQ-5D) [54]. The EQ-5D comprises 5 dimensions (mobility, self-care, usual activities, pain/discomfort, anxiety/depression). Health states defined by the 5-dimensional system are converted into a weighted health state index by applying scores from “value sets” elicited from general population samples. Following recommendations of the Panel on Cost-effectiveness in Health [55], quality-adjusted life years (QALYs) is used as the measure of effectiveness. QALYs are determined by estimating the utility value for several pain categories ranging from severe pain (KOOS ≤25 on 0–100 scale) to no pain (KOOS ​= ​100), each category will have utility value. The utilities will also depend on the number of comorbidities and obesity class [56].

We discount costs and effectiveness valuations 3 ​% per year. The cost-effectiveness analysis covers the trial duration and the remaining lifetime. The lifetime analysis will involve projecting outcomes and costs beyond the course of the trial using the validated OAPol model [51,57,58].

### Statistical considerations

3.12

#### Data management

3.12.1

The Data Coordinating Center has primary responsibility for randomization, quality control, and analyses of data generated by the clinical centers. Most participant data are collected with direct entry into the study electronic data capture system. In some instances (e.g., dietary screener) data are collected electronically at each center and transferred to the database. The web-based management system (PatientIQ) assures integrity and validity. Only specific Data Coordinating Center and Clinical Coordinating Center personnel have access to the data, with restrictions by site and study role. Dynamic reports and periodic statistical analyses monitor quality. A participant inventory system tracks recruitment, retention, adherence, and missing data from entry through exit, close-out, and lock-down of data.

#### Statistical analysis

3.12.2

##### Primary outcome

3.12.2.1

The primary hypothesis of reduced long-term risk of MRI-based OA is tested using a modified Poisson regression model [59] where OA presence (tibiofemoral and/or patellofemoral OA) at 48 months is the binary outcome and treatment assignment as the main predictor, adjusted for randomization strata, clinical center, and baseline BMI [59]. The modified Poisson regression model focuses on relative risk. Unlike logistic regression, which may produce invalid relative risk estimates, the modified Poisson procedure permits robust variance estimation and allows unbiased estimation of both model-adjusted relative and absolute risk, per CONSORT guidelines [60]. Currently, the modified Poisson regression model does not handle clustered data, although it is possible that participants within a clinical center are more similar than participants across centers. A sensitivity analysis will use logistic regression (OA or no OA as binary outcome) with mixed effects (with random effect for treating center as cluster) to the data. The primary treatment effect is tested using a 2-tailed Likelihood Ratio test assuming a Type I error rate of 0.05. Participants are analyzed according to their randomized group in accordance with intent-to-treat principles.

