### Trial organization

2.1

The intervention is delivered in four centers in the United States and Australia. Clinical and Data Coordinating Centers oversee the day-to-day operation of the trial. The Executive Committee [Principal Investigator (PI), site PIs] is responsible for major policy and budgetary decisions that govern the conduct of the trial. An advisory board composed of females at risk for knee OA, health providers, public and private arthritis organizations, and industry ensures strong input from a variety of stakeholders.

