### Randomization and masking procedures

3.3

Each eligible participant is randomized with a 1:1 allocation ratio to either a dietary weight loss, exercise, and weight-loss maintenance intervention or a control group using a permuted block randomization approach with random block sizes and stratified by intervention site to ensure balanced allocations within sites and obesity categories. A web-based randomization system will determine group assignment. Outcome assessors will remain blinded throughout the trial with no access to participants during intervention visits.

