#### Recruitment

3.9.1

The recruitment goal for each center was based on previous recruitment successes; Chapel Hill, Winston-Salem, Boston, and Sydney preliminary recruitment goals are 300, 360, 250, and 320, respectively (total ​= ​1230). Based on our mock recruitment and previous recruitment experiences, we estimate an average yield (number randomized divided by the number who expressed interest in the study) of 13 ​% (Table 3). A web-based data tracking system will monitor recruitment strategies at each center.

**Table 3 tbl3:** Preliminary recruitment projections.

Inquiries	Eligible after prescreening	Eligible after Screening Visit 1 including X-ray	Eligible after Screening Visit 2 including MRI	# Randomized
9110	2733 (30 ​% of inquiries)	1640 (60 ​% of pre-screened)	1230 (75 ​% of SV1)	1230 (13 ​% of inquiries)

Inquiries is defined as the number of people who expressed interest in the study.

The four center project managers and the coordinating center staff will coordinate recruitment efforts at each clinical center. Recruitment methods include mailings, local newspaper ads, hospital patient databases, and social media platforms. We also have strong partnerships with worksites in each community, access to churches, and a large database of adults aged ≥50 years who have signed consent to be contacted about participating in future clinical trials at each center. The Clinical Coordinating Center will build and maintain a study website and web-based tracking system where data at each center are entered in real-time for review of adherence to recruitment goals, intervention adherence, and study retention.

New participants are enrolled in the trial in waves approximately every 3 months during the recruitment period. The use of waves, as opposed to starting participants in their respective interventions as soon as they are randomized, promotes a group dynamic that is designed to enhance adherence to the intervention and retention in the trial [31]. Overall, the goal is to enroll an aggregate of 246 participants per wave for five waves.

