#### Screening radiograph and MRI

3.10.1

To be eligible for participation, subjects must have at least one knee free of radiographic and MRI evidence of knee OA. Bilateral posteroanterior (PA) weight-bearing knee x-rays using a positioning device and the modified Lyon-Schuss technique [34] will be used to identify tibiofemoral (TF) OA and skyline views to identify patellofemoral (PF) OA. We will exclude potential participants with bilateral PF OA [Joint Space Narrowing (JSN) ​≥ ​2 on OARSI scale, definite osteophytes on the lateral and/or medial patella [35]] or TF OA (Kellgren-Lawrence score (KL) ​≥ ​2) [36]. For two eligible knees, a hierarchal approach using the TF score (KL 1, 0), PF score (1, 0), and pain (most symptomatic) will determine the index knee for MRI analysis. The dominant leg will be selected if x-ray and pain are equal. For x-rays that indicate no or doubtful knee OA (KL ​≤ ​1), the absence or presence of MRI-defined OA is determined using the Rapid OsteoArthritis MRI Eligibility Score (ROAMES) semi-quantitative scoring system (note: the ROAMES is used to assess eligibility only) [37]. If the most at-risk knee is not eligible after the MRI, the other knee may be reassessed. Based on the Prevention of Knee Osteoarthritis in Overweight Females (PROOF) trial, 20 ​% of those who pass the x-ray will present with MRI-based knee OA and be ineligible for randomization [38,39].

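### The primary model leaves out baseline index-knee status recorded at screening; adding it is a cheap, modest gain, and the strata wording should be tidied in the same edit

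*Protocol article*

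**What the plan says.** **Primary model (3.12.2.1, Primary outcome).** A modified Poisson regression of OA presence at 48 months on treatment is "adjusted for randomization strata, clinical center, and baseline BMI". No knee-level baseline variable is listed.

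**Baseline knee data (3.10.1, Screening radiograph and MRI).** Eligibility is decided per knee: "subjects must have at least one knee free of radiographic and MRI evidence of knee OA". When both knees qualify, "a hierarchal approach using the TF score (KL 1, 0), PF score (1, 0), and pain (most symptomatic) will determine the index knee". The section treats the knee so chosen as the one at greatest risk. All of this is known before randomization.

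**Randomization (3.3).** "Each eligible participant is randomized with a 1:1 allocation ratio", in permuted blocks, "stratified by intervention site to ensure balanced allocations within sites and obesity categories". Site is the only factor named. Section 2.1 says "The intervention is delivered in four centers in the United States and Australia".

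**Sample size (3.13).** Control risk at 48 months 27.1%, a 30% relative reduction, 80% retention, 615 randomized and 492 evaluable per arm, 85% power, two-tailed chi-squared test at 0.05. No covariate gain is assumed.

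**The concern.** Every index knee is free of MRI-defined OA at entry, so the baseline value of the outcome is constant and cannot serve as a covariate. The nearest substitutes are KL grade, patellofemoral score and pain. The secondary models (3.12.2.2) adjust for the baseline value of each outcome; the primary model has no counterpart. If the screening markers predict incident OA, leaving them out gives up some precision and leaves the primary comparison open to chance imbalance in them.

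The covariate list has a separate wording problem. If the strata are the sites and the sites are the centers, one variable is listed twice. If obesity category is also a stratification factor, 3.3 does not say so. If it is not, stratifying by site cannot ensure the balance within obesity categories that 3.3 claims.

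**Working it through.** **1. The plan's own figure.** Inputs from 3.13: p1 = 0.271; p2 = 0.7 × 0.271 = 0.1897; n = 492 per arm.

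- The standard two-proportion formula at 85% power gives 481 per arm, or 505 with continuity correction. The stated 492 lies between them, and 492/0.80 = 615.
- Power of the two-proportion test at 492 per arm is 0.858.
- On the scale of the planned model, the robust variance of the log risk ratio is [(1−p1)/p1 + (1−p2)/p2]/n = (2.690 + 4.271)/492 = 6.962/492, so SE = 0.1190. Then 0.3567/0.1190 = 2.998, and power = Φ(2.998 − 1.960) = 0.850.

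The 85% reproduces without any covariate.

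**2. Gain from one binary knee covariate.** Let s be the share of index knees at KL 1 and r the risk ratio of KL 1 to KL 0. **Both are assumptions; the documents give neither.** Control-arm risk is held at 0.271 overall and r is the same in both arms. In the modified Poisson model each arm's variance contribution falls from (1/p − 1)/n to (1/p − 1 − CV²)/n, where

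CV² = s(1−s)(r−1)² / (1−s+sr)².

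The ratio of adjusted to unadjusted variance is therefore 1 − 2CV²/6.962. Example, s = 0.3 and r = 3: CV² = 0.21 × 4/1.6² = 0.328; ratio = 1 − 0.656/6.962 = 0.906; SE = 0.1190 × √0.906 = 0.1132; power = Φ(0.3567/0.1132 − 1.960) = 0.883.

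The simulation columns come from the modified Poisson model with robust variance, 492 per arm, 4000 replicates per row, fitted with and without the covariate.

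| s | r | Variance ratio, formula | Variance ratio, simulated | Power, formula (0.850 unadjusted) | Power, simulated |
|---|---|---|---|---|---|
| 0.3 | 1.0 | 1.000 | 1.000 | 0.850 | 0.865 → 0.866 |
| 0.3 | 1.5 | 0.989 | 0.989 | 0.854 | 0.857 → 0.860 |
| 0.3 | 2.0 | 0.964 | 0.965 | 0.863 | 0.857 → 0.869 |
| 0.3 | 3.0 | 0.906 | 0.906 | 0.883 | 0.857 → 0.889 |
| 0.5 | 1.0 | 1.000 | 1.000 | 0.850 | 0.858 → 0.858 |
| 0.5 | 1.5 | 0.989 | 0.988 | 0.854 | 0.862 → 0.865 |
| 0.5 | 2.0 | 0.968 | 0.968 | 0.862 | 0.864 → 0.875 |
| 0.5 | 3.0 | 0.928 | 0.928 | 0.875 | 0.859 → 0.877 |

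The simulated ratios are of mean robust variances. The ratio of empirical variances of the estimates is 0.911 and 0.941 in the two r = 3 rows, hence 6-9% at r = 3. The comparison model holds treatment only, so if KL grade is correlated with BMI or center, which are already in the model, the added gain is smaller.

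**3. Site listed twice.** One data set of 984 was simulated with four sites in the target proportions ("preliminary recruitment goals are 300, 360, 250, and 320, respectively") and fitted by modified Poisson.

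| Terms beside treatment and BMI | Columns | Rank | log RR | SE |
|---|---|---|---|---|
| Site | 6 | 6 | −0.4814 | 0.1195 |
| Site, entered twice | 9 | 6 | −0.4814 | 0.1195 |
| Site × 3 obesity categories (assumed) | 14 | 14 | −0.4903 | 0.1196 |
| The same, plus site again | 17 | 14 | −0.4903 | 0.1196 |

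The repeated columns are aliased. Once they are handled, estimate and SE do not move.

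**4. Balance by obesity category under site-only stratification.** The 95% range of the chance difference between arms in a category's share π is ±1.96√(2π(1−π)/615): ±4.5 percentage points at π = 0.2 and ±5.6 at π = 0.5 (π assumed). Balance is therefore expected but not ensured.

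**The case against.** The strongest reply is that nothing here is an error. The covariate set is valid, the trial is sized on an unadjusted test, and further prognostic covariates are often left to an analysis plan that is not shown. That stands, and it is why the point is offered as an improvement.

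A second reply is that the hierarchy in 3.10.1 ranks two knees of one woman. It does not say that women with a KL 1 knee have two or three times the incidence of women with a KL 0 knee once MRI-defined OA has been excluded. That also stands. Knee pain is restricted further by eligibility, which allows only no or infrequent pain. The three markers are plausible predictors by the plan's own choice, but of unknown strength. A reader might infer that the plan gives up worthwhile precision at no cost; the documents do not show this, since at r = 1.0 there is no gain.

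On the wording, a reader might infer that the model is over-specified however 3.3 is read. It is not: strata could mean obesity category, entered as a main effect beside center and continuous BMI, and that model has full rank. Duplication follows only if the strata are the sites themselves or crossed site-by-category cells. The article also does not define whether an intervention site is the same thing as a clinical center. Adjusting for baseline BMI further limits what any imbalance in obesity category could do to the primary result.

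**Conclusion.** The primary model omits baseline knee variables that the trial already collects and itself uses to rank risk. Prespecifying them is a cheap improvement with an uncertain, modest return. For KL grade alone the variance of the log risk ratio falls by 0% to about 9%, and power rises by 0 to about 3 points. This rests on an assumed KL 1 share of 30-50% and an assumed risk ratio of 1 to 3. The other two markers were not quantified. Adjustment also protects against chance imbalance in whichever markers do predict OA.

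The stated 85% power and 615 per arm are not in error on this account. The mismatch between 3.3 and 3.12.2.1 is a matter of clarity, with no effect on the estimate or SE where site is simply repeated.

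**What to change.** In 3.12.2.1 and the analysis plan, before unblinding, list each covariate once:

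- clinical center;
- obesity category, only if randomization was stratified on it;
- continuous baseline BMI;
- index-knee KL grade (0 or 1);
- index-knee patellofemoral score (0 or 1);
- baseline knee-pain status of the index knee.

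In 3.3, state the stratification as programmed: either name obesity category as a factor and give its cut-points, or delete the claim of balance within obesity categories. Say whether intervention site and clinical center are the same unit.

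The cost is wording plus three extra prespecified terms. No new data are needed and the sample size does not change.
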